### Data Collection and Quality Control

Thorough recording of all data will be performed on CRFs subsequent to in-person visits or telephonic communications with participants. The same examiner will assume responsibility for conducting the examination of every patient during each assessment. Baseline measurements, demographics, medical history, and prior medications will only be gathered during the initial visit. Primary outcomes, secondary outcomes, and safety indicators will be gathered at baseline and 4 weeks thereafter. Following adequate training and successful completion of a test, 2 data entry clerks will thoroughly review the CRFs and subsequently enter the collected data independently. Participants’ personal information will be kept confidential the same way as their medical histories in the hospitals before, during, and after the trial. The absence of a data monitoring committee in this study is justified by the anticipated low incidence of AEs and the limited participant numbers at each center. The Epidata 3.1 statistical application will be used for data entry. Subsequently, the collected data will be transferred to IBM SPSS 22.0 statistical software for the purpose of analysis.

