**Methods:**

In total, 192 participants aged 18-75 years with GPCI from the Mianyang Central Hospital, the Mianyang Hospital of Traditional Chinese Medicine, and the Mianyang Wanjiang Eye Hospital will participate in this study. Participants will be allocated to 2 treatment groups (experimental and control groups) in a ratio of 1:1 and will undergo press-needle therapy and sham press-needle therapy, respectively, for the same 4-week period. Primary outcomes will include the best-corrected visual acuity (BCVA), optical coherence tomography angiography (OCTA), color Doppler flow imaging (CDFI), and visual field assessment results. Secondary outcomes will include the intraocular pressure (IOP) and traditional Chinese medicine (TCM) clinical symptom scales. The primary outcomes and safety assessments will be measured at baseline and 4 weeks thereafter, while the secondary outcomes will be measured at baseline and 1, 2, 3, and 4 weeks thereafter.

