#### Criteria for Discontinuing or Modifying Allocated Interventions

Participants will have the freedom to withdraw from the clinical study and opt for alternative treatments (eg, citicoline sodium tablets) if they believe their condition will not improve. Reasons for discontinuing treatment may include, but are not limited to, the following: (1) the pregnancy, (2) severe side effects or complications, (3) taking other medications during the study, (4) failure to comply with the study protocol, and (5) request for withdrawal for other reasons.

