#### Secondary Outcome Measures

The following secondary outcomes will help us determine whether press-needle therapy improves TCM clinical symptoms and changes in the IOP:

The mean change in the IOP in the study eye will be determined uisng a TX-20P full autotonometer at baseline and at 1, 2, 3, and 4 weeks thereafter.Changes in TCM symptoms will be assessed by the investigators trained in SOPs according to the TCM Symptom Score Scale (Table S1 in Multimedia Appendix 1) at baseline and at 1, 2, 3, and 4 weeks thereafter.

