### Sample Size Calculation

The sample size calculation was based on previous studies. The basis of optic nerve protection effectiveness is 70% [16,17]. We hypothesized an 80% effective rate of the basis of optic nerve protection + press needles for GPCI in a larger sample size. According to the sample size of the estimation formula [18], α=.05 and β=0.10 in a 2-sided test, *P*_1_=.67 and *P*_2_=.87, 2-sided u_α/2_=u_0.05/2_=1.96, and 1-tailed u_β_=u_0.1_=1.282. We substituted these values into the following formula:

This resulted in n^1^=n^2^=79.02, that is, approximately 80 cases each in the experimental and the control group, or 160 cases in both groups. To account for a 20% dropout rate, the calculation 160 + (160 × 20%) = 192 suggested that 192 patients be recruited.

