### Statistical Analysis

Statistical analysis will be conducted independently by statisticians. The data will be presented as means (SDs). IBM SPSS 22.0 statistical software will be used. All statistical tests will be 2-sided tests, and the limit for statistical significance will be set at *P*<.05. The chi-square test will be performed for categorical variables, the independent Student *t* test will be used for measurement data, and the rank-sum test will be used for grade data. To evaluate the covariate balance, baseline characteristics will be summarized and compared between the experimental group and the control group using simple descriptive statistics.

Due to the expected low number of missing data, we will deal with missing data by transferring the last data item to the final dataset. This participant's data will be invalidated in the full analysis set (FAS), and this case will not be included in the per protocol set (PPS). Finally, the statistical significance of the FAS and PPS will be analyzed. A consistent statistical significance will indicate a significant difference.

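### The visit schedule for the two secondary outcomes is stated in two ways, and on either one the carry-forward rule biases the full-analysis-set estimate for the TCM symptom score (minor)

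*Protocol article*

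**What the plan says.** **Schedule.** The Abstract (Methods) separates the secondary outcomes from the primary ones: "while the secondary outcomes will be measured at baseline and 1, 2, 3, and 4 weeks thereafter". Secondary Outcome Measures repeats this for each outcome. IOP is measured with a "TX-20P full autotonometer at baseline and at 1, 2, 3, and 4 weeks thereafter", and TCM symptoms are assessed "according to the TCM Symptom Score Scale (Table S1 in Multimedia Appendix 1) at baseline and at 1, 2, 3, and 4 weeks thereafter". Data Collection and Quality Control puts all classes of outcome on one schedule: "Primary outcomes, secondary outcomes, and safety indicators will be gathered at baseline and 4 weeks thereafter".

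**Missing data.** Statistical Analysis expects few missing values and states that "we will deal with missing data by transferring the last data item to the final dataset". It adds that such a participant's "data will be invalidated in the full analysis set (FAS), and this case will not be included in the per protocol set (PPS". The FAS and the PPS are both analysed, and a difference counts as significant only if the two agree.

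**Loss to follow-up.** Sample Size Calculation adds patients with the words "To account for a 20% dropout rate". The discontinuation criteria let participants leave for another treatment "if they believe their condition will not improve".

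**The concern.** A carry-forward rule is only as definite as the list of visits it draws on. With weekly visits, someone who leaves after week 1, 2 or 3 contributes that week's value. With baseline and week 4 only, there is nothing to carry except baseline, so the change is exactly zero. One written rule thus describes two analyses of the same outcome.

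Neither version is neutral. If patients improve over the four weeks, a value carried from an earlier visit understates what would have been seen at week 4. With equal losses, this shrinks a true difference between arms. With unequal losses, it favours the arm that keeps more people. Unequal loss is conceivable here, because participants may leave when they expect no improvement.

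The TCM symptom score is the outcome mainly at risk. If IOP has no trend, carrying either value leaves its mean change near zero. The primary outcomes are outside the conflict, since every statement gives them baseline and week 4 only.

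**Working it through.** The plan states no figure that depends on this point, so there is none to reproduce. The check compares the texts and then illustrates the consequence.

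**Step 1: the texts.** The Abstract and Secondary Outcome Measures agree on weekly visits. The data-collection sentence names secondary outcomes and gives two time points. The article uses the same two-point phrase for primary outcomes and safety tests, where it plainly means two visits. No text shown reconciles the two.

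**Step 2: inputs.** From the protocol: 192 patients, 96 per arm, and 160 needed after losses. The planned loss is 192 − 160 = 32, so 32/192 = 16.7%, or 16 per arm. Assumed, because the documents give no TCM score mean, SD or dropout pattern:
- improvement is linear over four weeks;
- those who leave are equally likely to have baseline, week 1, 2 or 3 as their last visit;
- within each arm, dropout is unrelated to outcome.

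The mean share of the week-4 change reached at the last visit is then (0 + 0.25 + 0.50 + 0.75)/4 = 0.375.

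**Step 3: equal loss d in both arms.** Share of a true difference kept = 1 − d with baseline carried, and 1 − (1 − 0.375)d = 1 − 0.625d with the weekly value carried.

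| d | Baseline carried | Weekly value carried |
|---|---|---|
| 16.7% | 0.833 | 0.896 |
| 20% | 0.800 | 0.875 |

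If nobody leaves before week 1, the mean share reached is 0.5, and at 20% loss the figures are 0.80 and 1 − 0.5 × 0.20 = 0.90.

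**Step 4: unequal loss, no true difference.** Take 24 of 96 lost v 8 of 96, with both arms improving by M. False difference = M × (24 − 8)/96 = 0.167M with baseline carried, and 0.625 × 0.167M = 0.104M with weekly values carried.

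| M (SD) | Baseline carried (SD) | Weekly value carried (SD) |
|---|---|---|
| 0.5 | 0.08 | 0.05 |
| 1.0 | 0.17 | 0.10 |
| 1.5 | 0.25 | 0.16 |

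If improvement comes early (60%, 80%, 95% and 100% of a 1 SD total by weeks 1 to 4), the mean share reached is (0 + 0.60 + 0.80 + 0.95)/4 = 0.5875. The weekly version then gives (1 − 0.5875) × 0.167 = 0.07 SD, against 0.17 SD with baseline carried.

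**Step 5: significance.** Simulation: 20,000 trials, change SD 1 at each week, correlation 0.6 between weeks, two-sided t test at 5%, and the losses of step 4. With no true difference, the rejection rates are:

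| M (SD) | FAS alone, baseline carried | FAS alone, weekly carried | FAS and PPS both significant |
|---|---|---|---|
| 0.5 | about 9% | about 6% | about 3% on either schedule |
| 1.0 | about 20% | about 10% | about 3% on either schedule |
| 1.5 | about 35% | about 16% | about 3% on either schedule |

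Observed week-4 values alone give 5% in every case. With equal loss of 16 per arm and a true difference of 0.47 SD, FAS power is about 82% (baseline) v 83% (weekly).

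**The case against.** **The decision rule protects the trial's conclusion.** A reader might infer from the FAS-only rates that the trial could declare a false difference 20% or 35% of the time. The documents do not support that. Significance needs agreement between the FAS and the PPS, and participants with missing data are left out of the PPS. The PPS test therefore holds the joint rate at or below about 5%, and it comes out near 3%. This objection stands in full as to declared differences, provided dropout is unrelated to outcome within arm. It does not repair the FAS estimate, its confidence interval or its own P value.

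**The schedule is probably weekly.** A reader might also infer that the schedule is truly undetermined, or that the two outcomes are measured only twice. Two specific statements agree on weekly visits, the conflicting sentence does not say only, and the schedule table and flowchart are not shown. What was recorded on the CRFs, not a summary sentence, fixes what can be carried. This makes the weekly column the relevant one, but that column still shows bias.

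**Carried values may not be used at all.** If invalidating a participant's data in the FAS means dropping the carried value, the bias does not arise. The carry-forward sentence would then have no purpose, so the text needs settling either way.

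**The inputs are unfavourable.** A 24 v 8 split has no source, and subjects are blinded to a sham control. The article also reports 192 of 220 as completers, a loss of 28/220 = 12.7%. At that loss, equal in both arms, the share kept is 0.873 (baseline) or 1 − 0.625 × 0.127 = 0.920 (weekly), so the effect is smaller but not absent. The unequal case shows what could happen and is not a forecast.

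**Conclusion.** The contradiction is in the current text, and weekly collection is the more likely intention. Carry-forward as written biases the FAS estimate of the week-4 TCM score difference on either schedule, and more if only baseline is available. About 90% (weekly) v 83% (baseline) of a true difference is kept at equal loss of 16 per arm. A false difference of about 0.10 v 0.17 SD appears if losses are 24 v 8 and both arms improve by 1 SD. These sizes rest on assumed linear improvement, evenly spread last visits and dropout unrelated to outcome within arm.

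The point concerns one secondary outcome in the main, with little effect on IOP and none on the primary outcomes. It does not raise the rate at which the trial declares a difference, and power hardly changes with equal loss. It falls away if carried values are not used in the FAS. Severity: minor.

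**What to change.** 1. **Data Collection and Quality Control.** After checking the CRFs, state that primary outcomes and safety tests are collected at baseline and week 4, and that IOP and the TCM symptom score are collected at baseline and weeks 1, 2, 3 and 4.
2. **Statistical Analysis.** For these two outcomes, compare arms at week 4 in the FAS with a mixed model on all observed weekly values, with baseline as covariate. The named SPSS software can fit it. Keep carry-forward only as a sensitivity analysis and define the carried value as the last attended weekly visit. Reword the sentence on invalidated data so that it is clear which values enter the FAS.
3. **Reporting.** Give, by arm, the number of missing week-4 values and the last week attended. Participants with no visit after baseline add nothing to this model, so their number should be visible.

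If the CRFs turn out to hold only baseline and week 4, correct the Abstract and Secondary Outcome Measures instead, and compare observed week-4 values adjusted for baseline without carrying baseline forward.

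The cost is one corrected sentence, a few sentences on analysis and a small table. No new visit, test or CRF item is needed. The change can be made before the analysis planned for October 2025, while the statisticians are blinded. The downside is that a mixed model assumes dropout depends only on observed values, which the data cannot prove.

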### Sample Size Calculation

The sample size calculation was based on previous studies. The basis of optic nerve protection effectiveness is 70% [16,17]. We hypothesized an 80% effective rate of the basis of optic nerve protection + press needles for GPCI in a larger sample size. According to the sample size of the estimation formula [18], α=.05 and β=0.10 in a 2-sided test, *P*_1_=.67 and *P*_2_=.87, 2-sided u_α/2_=u_0.05/2_=1.96, and 1-tailed u_β_=u_0.1_=1.282. We substituted these values into the following formula:

This resulted in n^1^=n^2^=79.02, that is, approximately 80 cases each in the experimental and the control group, or 160 cases in both groups. To account for a 20% dropout rate, the calculation 160 + (160 × 20%) = 192 suggested that 192 patients be recruited.

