However, the fear of acupuncture pain or the limitations of the treatment place and time lead to poor patient compliance. Press-needle acupuncture is one kind of acupuncture that has a longer treatment duration and simpler operation with less pain [9]. The theoretical basis of press-needle therapy is the combination of acupuncture theory and skin meridian and acupoint theory. *Suwen: Treatise on the Dermis* states that “all twelve meridians are also part of the skin” and that “the skin is closely related to the veins. The skin is also part of the pulse.” The dermis is connected with the 12 meridians by qi and blood. Through the 12 meridians, the 12 dermises are in close contact with the 5 viscera, 6 internal organs, and the eye orifices, forming a coordinated and unified organic whole. Press-needle therapy has been widely used to treat glaucoma with controlled intraocular pressure (GPCI), but useful empirical research is insufficient for its popularization and application. The disadvantages of less rigorous designs, small sample sizes, and low quality have led to many traditional Chinese medicine (TCM) studies being insufficient to convince people of its value.

Hence, a randomized, sham-controlled trial will be conducted to assess the potential of press-needle therapy in improving visual function and eye blood circulation in patients with GPCI.

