### Interventions

#### Experimental Group

Acupoints will be selected based on acupuncture combined with clinical experience [15]: main acupuncture points (BL2 Cuanzhu, TE23 Sizhukong, EX-HN5 Taiyang, and ST2 Sibai) and matching points (PC6 Neiguan, SP10 Xuehai, BL17 Geshu, BL18 Ganshu, BL23 Shenshu, SP6 Sanyinjiao, and K13 Taixi) (Figure 1). These points can exert a concerted effect to nourish the liver and kidneys, promote blood circulation, and dredge collaterals. Press-needle treatment will be performed by acupuncturists with more than 3 years of clinical experience. The acupuncturist will disinfect the skin around the acupoints (on the same side of the affected eye) with povidone iodine when the subject lies down on the treatment bed in a supine position. Disposable sterile press needles (0.2 mm in diameter and 0.6 mm in length; Seirin Corporation) will then be inserted into the right acupoints (Figure 1). The needles will be pressed so that they can adhere and be tied, the peelable paper will be removed, and the adhesive tape will be pressed down to ensure a secure fit. The needles will be left in place for 2 days, and participants will be asked to press the needles themselves 3-4 times/day, every 4 hours, for 1 minute each time to achieve deqi sensations, including soreness, numbness, heaviness, fullness, and aching.

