#### Control Group

Sham press needles are the same as press needles but lack the needle element [9]. The procedures and manipulations carried out in the control group will be indistinguishable from those implemented in the experimental group. Subjects will be treated individually in a secluded room to prevent any disruptions from family members or other individuals.

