### Conclusion

In conclusion, the purpose of this research is to verify that press-needle therapy can effectively improve visual function and eye blood circulation in patients with GPCI. The outcome of this study will provide evidence-based data for the use of press-needle therapy to treat GPCI accompanied by liver-kidney deficiency, blood stasis, and fluid retention syndrome, thereby providing a new avenue for the treatment of GPCI.

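### The sample size sets background care alone against background care plus press needles, but the trial randomizes against background care plus sham, and the stated 90% power is not established for that contrast or for the protocol's own inputs

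*Protocol article*

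**What the plan says.** The Sample Size Calculation describes two quantities. For background treatment it says: "The basis of optic nerve protection effectiveness is 70" percent. For the experimental side it says: "We hypothesized an 80% effective rate of the basis of optic nerve protection + press needles for GPCI in a larger sample size". It then fixes "α=.05 and β=0.10 in a 2-sided test", enters .67 and .87 without tying either to an arm or a source, and obtains 79.02 per group. This is rounded to 80 per group and raised by 20% to 192 in total.

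The Discussion (Overview) identifies the background drug as methylcobalamin, given to both arms, and says that a sham press needle was chosen as the control. The Blinding and Control Group sections describe a non-penetrating device of the same appearance without the needle. On handling, the Control Group section says: "The procedures and manipulations carried out in the control group will be indistinguishable from those implemented in the experimental group".

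The outcomes sections list changes in visual acuity, perimetry, OCTA and Doppler measures as primary, and intraocular pressure and a symptom scale as secondary. An effective rate is not among them. The Conclusion gives the aim as follows: "the purpose of this research is to verify that press-needle therapy can effectively improve visual function and eye blood circulation in patients with GPCI".

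**The concern.** The sized contrast is background versus background plus press needles. The randomized contrast is background plus sham versus background plus press needles. The two coincide only if the sham adds nothing to the response rate, and the protocol neither states nor supports that. An ordinary placebo response in the sham arm would raise the control rate, shrink the difference that was sized, and lower the power. A reader who takes 90% at face value would then give a null result more weight than the design supports.

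The same section also contradicts itself on the rates (70% and 80% in the text, .67 and .87 in the calculation). It is therefore unclear which background rate a sham response would be added to.

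**Working it through.** **Inputs.** All come from the Sample Size Calculation unless noted: two-sided alpha .05 (1.96), beta .10 (1.282), rates .67 and .87, 80 per arm, total 192. Allocation is 1:1 (Randomization and Allocation). The Results section expects 192 to complete, which is 96 per arm if balanced. The response rate under background plus sham is not given. .67 is read as the control rate, which the section implies but does not say.

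**Step 1: the plan's own figure.** The formula itself is missing from the text available here, so the usual pooled form was used:

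n = [1.96·s0 + 1.282·s1]² / (p2 − p1)², with s0 = √(2p̄(1−p̄)) and s1 = √(p1(1−p1) + p2(1−p2)).

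For .67 and .87: p̄ = .77, s0 = √.3542 = .5951, s1 = √.3342 = .5781.

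n = (1.1665 + .7411)² / .04 = 90.97, so 91 per arm.

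Other two-sided forms give 87.8 (unpooled), 88.9 (arcsine), 93.1 (2p̄q̄ form) and 101 (continuity-corrected). A one-sided pooled test gives 74. None gives 79.02. The step 160 × 1.2 = 192 does reproduce.

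**Step 2: power on the protocol's inputs, with no sham response.**

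Power = Φ{[(p2 − p1)√n − 1.96·s0] / s1}.

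- .67 vs .87, 80 per arm: (1.7889 − 1.1665)/.5781 = 1.077, so 85.9%.
- .67 vs .87, 96 per arm: (1.9596 − 1.1665)/.5781 = 1.372, so 91.5%.
- .70 vs .80 (s0 = .6124, s1 = .6083), 80 per arm: (.8944 − 1.2002)/.6083 = −.503, so 30.8%. At 96 per arm: −.362, so 35.9%. About 392 per arm would be needed for 90%.

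**Step 3: sensitivity to a sham response.** The response is an assumption. The experimental rate is held at .87.

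| Assumed gain over .67 | Control rate | Power, 80 per arm | Power, 96 per arm | n per arm for 90% |
|---|---|---|---|---|
| 0 | .67 | 85.9% | 91.5% | 91 |
| 5 points | .72 | 65.4% | 73.4% | 151 |
| 10 points | .77 | 37.6% | 43.7% | 309 |

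Example: for .72, s0 = .5709 and s1 = .5610, so at 80 per arm (1.3416 − 1.1190)/.5610 = .397, which is 65.4%.

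A control rate of .70 against .87 gives 74.9% at 80 per arm. That row is left out of the table because .70 is the protocol's own background rate. The drop from 85.9% to 74.9% can come from the unreconciled inputs without any sham effect.

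**The case against.** The strongest reply is that a sham control is a sound choice, the trial is openly described as sham-controlled, and the document gives no evidence that this sham raises the response rate. Every loss in Step 3 is therefore conditional. Whether the studies behind the 70% already included a placebo or sham cannot be checked either. All of that stands. It means that the size of the loss is unknown, but the sizing text still describes a different contrast.

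A second reply is that 192 are expected to complete, so 96 per arm is the fairer basis. On .67 versus .87 with no sham response, 96 per arm does exceed 90%. This also stands, and both sizes are shown. It does not help under 70% versus 80%, or under an assumed 5-point response.

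Third, the effective rate is not a listed outcome, so even a corrected power figure says little about the primary comparisons. That is right, and the restated text should say so.

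A reader might go further and infer that the sham is active treatment. The Introduction says "The theoretical basis of press-needle therapy is the combination of acupuncture theory and skin meridian and acupoint theory" and links the skin through the meridians to the eye, and the Experimental Group section says "participants will be asked to press the needles themselves 3-4 times/day, every 4 hours, for 1 minute each time". But home pressing is described only for the experimental arm. That it extends to the control arm is an inference from the wording on procedures, and nowhere does the protocol say that pressing without a needle has an effect. A reader might also see an overclaim of whole-therapy efficacy. The protocol makes no such claim in those terms, and reporting efficacy against sham is conventional.

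**Conclusion.** The point holds in a limited form. The sizing takes its control rate from background treatment alone and allows for no sham response, so the stated 90% power is not established for the comparison the trial makes.

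It would be wrong to conclude that the 90% is valid for background alone versus background plus press needles. It is not established there either: 79.02 does not reproduce, 80 per arm gives 85.9% on .67 versus .87, and the rates in the text give 30.8%. Nor is .87 the rate that the text assigns to background plus press needles, which is 80%.

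Under the stated assumption (.87 held, control raised from .67), 5 points of sham response cost about 20 points of power at 80 per arm and 18 at 96. Ten points cost about 48 at either size. These figures show sensitivity and do not estimate what will happen. The wording of the efficacy claim is a lesser matter of interpretation.

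**What to change.** In the Sample Size Calculation:

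1. Name the contrast as background plus sham press needle versus background plus press needle.
2. Reconcile 70% and 80% with .67 and .87, and say which rate belongs to which arm and where it comes from.
3. State the assumed response rate under background plus sham.
4. Replace the single 90% figure with power at the existing size over a stated range of sham response, for example 0 to 10 points, and correct the 79.02.
5. Say that the effective rate used here is not among the listed outcomes, so this power does not carry over to the primary comparisons.

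In the objectives and the Conclusion, word the efficacy claim as the effect over sham press needles on top of methylcobalamin.

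The cost is a few sentences and a less favourable stated power. No extra enrolment is proposed, and treatment, visits, sham and blinding are unchanged.

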### Outcome Measures

#### Primary Outcome Measures

The primary outcomes will enable us to evaluate improvements in visual function, retinal blood circulation, and retrobulbar blood vessel circulation due to press-needle therapy. The outcomes will be as follows:

The mean change in the BCVA will be measured at baseline and 4 weeks thereafter.The mean change in the values of the pattern standard deviation (PSD), mean defect, and square root of loss variance (sLV) will be determined using an Octopus 900 perimeter at baseline and 4 weeks thereafter.The whole-image vessel density (wiVD), radial peripapillary capillary vessel density (RPCVD), superficial macula vascular density (smVD), parafoveal vessel density (paraVD), perifoveal vessel density (periVD), macular ganglion cell complex (mGCC), and peripapillary retinal nerve fiber layer (pRNFL) will be determined using optical coherence tomography angiography (OCTA) at baseline and 4 weeks thereafter.The ophthalmic artery (OA), central retinal artery (CRA), short posterior ciliary artery (SPCA), peak systolic velocity (PSV), end diastolic velocity (EDV), and resistance index (RI) will be determined using CDFI at baseline and 4 weeks thereafter.

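### The sample size rests on an undefined effective rate that is not an outcome of the trial, so its 90% power supports no listed endpoint, and 80 per arm does not give 90% for the rate either

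*Protocol article*

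**What the plan says.** The Sample Size Calculation section of the protocol article reasons entirely in rates. For basic treatment it says: "The basis of optic nerve protection effectiveness is 70" per cent. For the combination it says: "We hypothesized an 80% effective rate of the basis of optic nerve protection + press needles for GPCI". The error rates are "α=.05 and β=0.10 in a 2-sided test", which means 90% power. The proportions entered in the formula are .67 and .87. The result is given as "This resulted in n^1^=n^2^=79.02, that is, approximately 80 cases each", and dropout is added by "the calculation 160 + (160 × 20%) = 192".

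The Primary Outcome Measures section lists different quantities: visual acuity ("The mean change in the BCVA will be measured at baseline and 4 weeks thereafter"), three perimetric indices, seven OCTA parameters, and flow velocities and resistance index in three vessels by colour Doppler. The secondary outcomes are IOP and a TCM symptom score. Neither list contains a responder or effective rate, and the article gives no rule for calling a patient effectively treated.

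The Statistical Analysis section assigns tests by type of data: chi-square for categorical variables, rank-sum for grade data, and "the independent Student *t* test will be used for measurement data". No expected difference or SD is stated for any primary outcome.

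**The concern.** A power statement belongs to one endpoint, one effect size and one test. Here the endpoint used for sizing is not in the trial's outcome lists, and the endpoints in those lists have no effect size. The α, β and 80 per arm are therefore not connected to the comparisons the trial will report.

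Two things are at stake. If visual field or blood flow shows no difference, a reader cannot tell from the protocol whether a worthwhile effect was excluded or could simply have been missed. And an effective rate that has justified the sample size but has no definition leaves open how it would be derived if it were reported.

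**Working it through.** **1. The stated figure for the rate.** Inputs from the Sample Size Calculation section: p1 = .67, p2 = .87, z for two-sided .05 = 1.96, z for β = 1.282, equal arms. The formula is an image that is missing from the text available to me, so the standard forms were tried. The pooled form is

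n = [1.96·√(2·p̄·(1−p̄)) + 1.282·√(p1(1−p1) + p2(1−p2))]² / (p2−p1)²

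With p̄ = .77:
- √0.3542 = 0.5951 and √0.3342 = 0.5781
- n = (1.1665 + 0.7411)² / 0.04 = 3.639 / 0.04 = 90.97, so 91 per arm

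Other forms at two-sided .05 and 90% power give 87.8 (unpooled), 93.1 (2·p̄·(1−p̄) throughout), 88.9 (arcsine) and 101 (continuity-corrected). A one-sided test gives 74, and 80% power gives 69. None gives 79.02.

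**2. Power for the rate.** Solving the pooled form for power, z = [(p2−p1)·√n − 1.96·√(2·p̄·(1−p̄))] / √(p1(1−p1) + p2(1−p2)).

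| Rates | n per arm for 90% | Power at 80 per arm | Power at 96 per arm |
|---|---|---|---|
| .67 vs .87 (formula) | 91 | 86% | 91% |
| .70 vs .80 (text) | 392 | 31% | 36% |

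For .67 vs .87 at 80 per arm: z = (1.7889 − 1.1665)/0.5781 = 1.077, which is 86%. For .70 vs .80: n = (1.2002 + 0.7798)² / 0.01 = 392.

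**3. What the numbers can support for a continuous outcome.** Three evaluable sizes are considered, assuming equal arms:
- 96 per arm, if the 192 named in the Results section all complete
- 80 per arm, the calculated requirement
- 77 per arm, if 20% of 192 drop out (192 × 0.8 / 2 = 76.8)

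The normal approximation to the detectable standardized difference is (1.96 + 1.282)·√(2/n). At n = 80 this is 3.242 × 0.1581 = 0.513. The exact two-sample t calculation is slightly larger:

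| Evaluable per arm | Detectable at 90%, α .05 | Detectable at 90%, α .0025 |
|---|---|---|
| 96 | 0.47 SD | 0.63 SD |
| 80 | 0.52 SD | 0.69 SD |
| 77 | 0.53 SD | 0.70 SD |

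The last column is conditional. It assumes 20 primary measures (1 acuity + 3 perimetry + 7 OCTA + 3 vessels × 3 flow indices) and a Bonferroni correction, .05/20 = .0025. The protocol states neither.

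**4. Power over a range of true effects.** The documents give no effect size, so these are assumed. With 80 per arm at two-sided .05, power is 24% at 0.2 SD, 47% at 0.3 SD, 71% at 0.4 SD and 88% at 0.5 SD.

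**The case against.** *The trial may be adequately powered.* This stands. A reader might infer from the mismatch that the trial is underpowered for its primary outcomes. The documents do not support that: with no difference or SD, power is unstated, not shown to be low. At a true 0.5 SD it would be 87% even with 77 per arm.

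*Realised numbers may exceed 80 per arm.* This also stands in part. The Results section reports 220 recruited and 192 who will complete, which at face value is about 96 per arm and would bring .67 versus .87 to 91% power. The same section gives inconsistent recruitment dates, so the smaller sizes remain possible. More patients do not attach the rate to an endpoint, and for 70% versus 80% power would still be 36%.

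*A chi-square test is planned.* It is named only for categorical variables in general. No categorical efficacy endpoint is defined for it to test.

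*Tests are assigned by data type, not by outcome.* True. That the primary outcomes go to the t test is an inference, though a natural one for quantitative measures.

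*A rate chosen after the data are seen is speculation.* Fair. Ethical Considerations requires a new protocol version and ethics approval if outcomes or analyses change, and the Discussion keeps investigators, statisticians and assessors blinded until database lock. These safeguards reduce the risk, but they do not define the rate.

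*A separate analysis plan may fill the gap.* It could add a definition. It would not repair a sample size paragraph that is complete as published and conflicts with the outcome list in the same article.

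**Conclusion.** The point holds as a mismatch between the Sample Size Calculation section and the outcome lists. The stated 90% power is attached to an undefined rate that is not an outcome, so it supports none of the listed endpoints. At the planned 80 per arm it is also wrong for the rate: 86% for the proportions in the formula and 31% for those in the text. These two pairs contradict each other (a difference of 20 points against 10), and 79.02 follows from neither under any standard form tried.

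The conclusion goes no further. The detectable differences of 0.47 to 0.53 SD describe the design at a single two-sided .05 test. They do not say whether the true effects are smaller or larger. The figures at .0025 rest on an assumed count of 20 and an assumed correction, and multiplicity is a separate matter.

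**What to change.** Before database lock, rewrite the sample size paragraph:

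1. Withdraw the claim that 80 per arm gives 90% power through an effective rate.
2. Designate one of the listed continuous outcomes as primary. For it, state the evaluable number per arm, the two-sided alpha, the assumed SD of its week-4 change with a source, and the difference detectable with 90% power: 0.47 SD at 96 per arm, 0.52 SD at 80, 0.53 SD at 77. Convert this to that outcome's own units.
3. If several outcomes stay primary, state the multiplicity rule and use the adjusted alpha. With 20 measures and Bonferroni, for example, the figures become 0.63, 0.69 and 0.70 SD.
4. If an effective rate will be reported, define it now, with its threshold and analysis, as a secondary endpoint.

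The cost is a rewritten paragraph and, because a primary outcome is being designated, a new protocol version to the ethics committee under the protocol's own rule. No more patients are needed. The downside is that a stated power becomes a detectable difference, which may look less favourable.
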